## Abstract

**Background:**

Concurrent epidemics of HIV, depression, alcohol abuse, and partner violence threaten maternal and child health (MCH) in South Africa. Although home visiting has been repeatedly demonstrated efficacious in research evaluations, efficacy disappears when programs are scaled broadly. In this cluster randomized controlled trial (RCT), we examine whether the benefits of ongoing accountability and supervision within an existing government funded and implemented community health workers (CHW) home visiting program ensure the effectiveness of home visiting.

**Methods/Design:**

In the deeply rural, Eastern Cape of South Africa, CHW will be hired by the government and will be initially trained by the Philani Programme to conduct home visits with all pregnant mothers and their children until the children are 2 years old. Eight clinics will be randomized to receive either (1) the Accountable Care Condition in which additional monitoring and accountability systems that Philani routinely uses are implemented (4 clinics, 16 CHW, 450 households); or (2) a Standard Care Condition of initial Philani training, but with supervision and monitoring being delivered by local government structures and systems (4 clinics, 21 CHW, 450 households). In the Accountable Care Condition areas, the CHW’s mobile phone reports, which are time-location stamped, will be monitored and data-informed supervision will be provided, as well as monitoring growth, medical adherence, mental health, and alcohol use outcomes. Interviewers will independently assess outcomes at pregnancy at 3, 6, 15, and 24 months post-birth. The primary outcome will be a composite score of documenting maternal HIV/TB testing, linkage to care, treatment adherence and retention, as well as child physical growth, cognitive functioning, and child behavior and developmental milestones.

**Discussion:**

The proposed cluster RCT will evaluate whether routinely implementing supervision and accountability procedures and monitoring CHWs’ over time will improve MCH outcomes over the first 2 years of life.

**Trial Registration:**

ClinicalTrials.gov registration #NCT02957799, registered on October 26, 2016.

**Electronic supplementary material:**

The online version of this article (doi:10.1186/s13063-017-2074-5) contains supplementary material, which is available to authorized users.

## Background

Home visiting has been repeatedly demonstrated efficacious in improving maternal and child health (MCH) outcomes when delivered by nurses [1–3] and paraprofessionals in low- and middle-income countries (LMIC) [4–6]. Each dollar invested in maintaining MCH yields a nine-fold benefit [7, 8]. Yet, when home visiting is scaled by community health workers (CHW), the efficacy often disappears [9]. The Alma Alta Declaration has encouraged attempts to mount CHW interventions in all LMICs, and therefore the strategies needed to consistently implement high quality programs with efficacious outcomes are increasingly important. The proposed study aims to identify how supervision and accountability strategies improve MCH outcomes of home visits by CHW.

In South Africa, the challenges to secure positive child outcomes for MCH remain overwhelming. Between 26% and 30% of mothers are living with HIV (MLH) and, while only a small percentage of their children are going to be seropositive, the uninfected children of MLH have growth and immune function challenges. Approximately 25% of pregnant mothers drink alcohol while pregnant, yielding the highest rates of fetal alcohol syndrome disorder in the world (9.5%) [10–12]. Maternal depression is self-reported by approximately 15% of mothers and 6% report depressive symptoms likely to be clinically significant. In every country, maternal depression impacts on child growth and development lifelong [13–16]. Finally, approximately 16% of mothers experience intimate partner violence, which remains very stable over time [17–22]. These maternal challenges threaten the health of their children. For example, in some South African communities, approximately 17% of babies are born with low birth weights (<2500 g) and these infants will be at lifelong risk for multiple negative outcomes [23–25]. Clearly, the number and scope of the challenges mothers experience indicate the importance of broad, structural implementation of efficacious interventions to support pregnant mothers and that this support needs to be extended over the first 5 years of life.

While paraprofessional home visiting has been repeatedly demonstrated to be efficacious, it has not been scaled nor does it concurrently retain efficacy. African countries have the lowest per capita health budgets and fewest well-trained personnel globally [26–30]. Building the personnel capacity, especially by systematically implementing training and accountability structures, has rarely been addressed [28]. This protocol is targeted at filling this gap.

The Philani Intervention Model (PIM) is a non-government organization with a 30-year history of successful, non-stigmatizing, and sustainable home-based support for pregnant women and malnourished children [17, 21, 31–35]. Key components of the PIM are to recruit CHWs who are community role models, train the CHWs extensively, with ongoing in-service trainings, and to monitor the quality of all contacts with supervisors randomly dropping-in on each CHW’s home visits biweekly and reviewing charts weekly, using the charts to iteratively build on CHWs’ skills. Our planned trial will build on this model, seeing if existing government CHWs (not selected to be role models), can improve the quality of their skills and home visits with a significant impact on MCH outcomes.

Therefore, in this study, the PIM field coordinators and supervisors will assume supervision and support responsibilities for government-hired CHWs in a deeply rural setting in the Eastern Cape of South Africa. CHWs in the PIM are equipped with mobile phones to allow easy accountability; that is, a phone that has a time and location stamp on which the CHW provides ratings of the visit’s content, the skills utilized, child weight/height, and perceived impact. The standard supervision procedures used by PIM will be implemented with CHWs randomized to the PIM condition. Based on the Quality Implementation Model [36], MCH outcomes will be monitored over 24 months to examine if accountability improves CHW outcomes.

## Methods/Design

The Institutional Review Boards of the University of California, Los Angeles (UCLA; IRB#16-001362) and Stellenbosch University (#N16/05/064) have approved the study protocol. A Data Safety Monitoring Board will review interim analyses of the 6- and 15-month assessments prior to the collection of the primary outcome data at 24 months. Each adverse event is reported to both Stellenbosch and UCLA Institutional Review Boards and the Data Safety Monitoring Board. The study protocol was developed in accordance with the Standard Protocol Items: Recommendations for Interventional Trials (SPIRIT) and the populated checklist and figure have been provided (Additional file 1 and Fig. 1). Authorship will be based on standards outlined by the American Psychological Association [37].

**Fig. 1 Fig1:**
[figure not shown]
Schedule of enrollment, interventions, and assessments

### Setting

The OR Tambo District is a rural, hilly area in the Eastern Cape of South Africa accessible on a 150 km paved road east from Umtata and north of East London, with very high unemployment. The area is ancient tribal land, with the tribe allowing only minimal industrialization. Zithulele Hospital serves 130,000 families with nine local clinics. To reach clinics, a patient must cover large distances of hilly terrain either by walking or using the expensive and infrequent mini bus taxis. Aerial maps provided information on the density of each potential study area.

With the support of the District Health Officer, the team has documented the catchment areas of each CHW assigned to eight clinics in the catchment area of Zithulele Hospital. Data on access to electricity (8% in the region), water tanks (16%), flush toilets (few), distance from the road and the local clinics, and hilliness was used to identify areas of about 200 households each. The areas were matched by UCLA and all CHWs at each clinic (3–5 per clinic) were randomized to either (1) the Accountable Care (AC) condition, in which the PIM supervision and training models will be implemented (4 clinics, 16 CHW, 450 households); or (2) Standard Care (SC) by existing government supervisors and CHWs implementing home visits (4 clinics, 21 CHW, 450 households). Risk of contamination is very low given it is a deeply rural region with vast distances between villages and even homes. Figure 2 outlines the design of the randomized controlled trial (RCT), with the planned follow-up assessments by an independent team of assessors.

**Fig. 2 Fig2:**
[figure not shown]
Description of the RCT for area randomization by UCLA to one of two conditions

### Recruitment

Female research interviewers have been placed in each clinic to recruit all pregnant women and securing voluntary informed consent. Each recruiter covers one clinic in the AC and one clinic in the SC condition. The eligibility criteria to participate in the study will be living in the catchment area and not identified as psychotic or delusional based on the interviewer’s judgment. Exclusion criteria are inability to give informed consent, inability to converse with the interviewer or the CHW, and death of the mother or infant. After consent, an independent team of assessors will conduct the follow-up assessments at the mother’s home.

### Assessments

Independent assessments will be conducted by Stellenbosch University during pregnancy, within 3 months of birth, and at 6, 15, and 24 months post-birth. The PIM is a generalist model. Therefore, there is a cluster of both maternal outcomes and child outcomes. Table 1 summarizes these measures, with the source of the data to determine accomplishment (1) or not (0) of each outcome. Assessors will conduct interviews and gather additional information from health case files, as well as the child’s government-issued, Road-to-Health card. All data will be entered on mobile phones with preprogrammed responses and sent encrypted to a data center. Data for identification will be stored separately from the assessment data. Assessment data will be coded with personal identification numbers and will not include any personally identifiable data. De-identified assessment data will be available through a password-protected, cloud-based database and accessed by UCLA and Stellenbosch University for quality control and, later, analysis. The risk of gathering information with properly trained and supervised staff poses minimal risk to the proposed participants. There are no physical risks associated with participation.

**Table 1 Tab1:** Outcomes assessed independently during pregnancy, within 3 months of birth, and at 6, 15, and 24 months post-birth scored by the attainment (1) or not (0) of well-being from 10 indicators of maternal and child health

Outcome	Measure
For Mother	
Adherence to medical regimes	Clinic records and self-reports; for mothers living with HIV, there are six prevention of mother-to-child transmission tasks, re-engagement in HIV care post-birth, receipt and adherence to antiretroviral medications over the last week
Breastfed for 6 months (mixed ok)	Self-report and home observations
Alcohol use (AUDIT-C > 2)	Breathalyzer and self-reports
Mental health (EPDS > 13)	Self-reports
For Children	
Growth in height (< −2 SD)	Measurements; tape measures and measuring boards calibrated biweekly
Growth in weight (< −2 SD)	Measurements; scales calibrated biweekly
Adherence to medical regimes	Clinic records, self-report, including for diarrhea, immunizations, respiratory illnesses
Number of hospitalizations and clinic visits	Clinic records, self-reports
WHO Developmental scale in normal range	Assessment of child and maternal reports
Bayley scale in normal range (24 months only)	Assessment of the child
Child Behavior Checklist in normal range on all scales	Maternal reports

Alcohol Use Disorders Identification Test-Clinical Utility (AUDIT-C)

Edinburgh Perinatal Depression Inventory (EPDS)

### Primary outcomes

Self-reports, the Road-to-Health card, and real-time reports by CHWs on mobile phones and in folders will be sources of data. Data collected from the assessment team will always be the gold standard, compared to data from the CHWs. Observational data will be seen as more valid and reliable than maternal self-report data. In the detailed analyses of each outcome with more than one data source, a sensitivity analysis will be conducted to examine whether a different result would have been observed if a different informant had been used as the outcome measure. The existing CHW reporting system for the government is a log of visits, with little more information than indicating that a visit occurred. The implementation design will not allow this RCT to improve this system and a key aspect of this study is whether the monitoring and data-informed supervision make a significant difference on MCH outcomes.

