### Intervention

#### SC

All CHWs will receive a mobile phone and initial Philani training for conducting home visits. The CHW will visit the mothers twice monthly during pregnancy until children are 6 months and then monthly until the children reach 2 years of age. All mothers are asked to re-enroll annually with voluntary informed consent at each assessment. The initial messages to CHWs with pregnancy and new mothers and the first 6 months of life are (1) HIV testing, adherence to therapy for MLH, nevirapine at childbirth, hospital delivery, a single feeding method for 6 months, PCR infant HIV testing at 6 weeks, and MLH reengagement in care and adherence to medication; (2) breastfeeding solely for 6 months, monitored by charting growth at each visit, and problem solving on how and where to get food; (3) reducing and eliminating alcohol use; (4) getting the child grant; (5) engaging in pleasant activities and building a social network; and (6) attending clinic visits (four antenatal visits, Well-Child visits, immunizations). After the first 6 months, the CHW focuses on encouraging mothers to stimulate and support their children daily.

Households in the target areas will be visited by government-funded CHWs. This is currently the SC in the Eastern Cape in the wards adjacent to the Zithulele catchment area (although not in all of the Eastern Cape). The existing government-implemented training, monitoring, and supervision structures will remain in place with the only addition being an initial Philani training for conducting home visits. The geographic areas covered by each of the existing CHWs in two wards will be defined and all pregnant women coming to the clinics will be recruited with voluntary informed consent by paraprofessionals or the assessment team. CHWs in the SC will refer all mothers to local clinics for HIV, blood sugar, and pregnancy testing. The rates of visits and tests are available from clinic data and also will be individually collected by the assessment team.

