There will be a “flag system” to prompt the CHW and supervisor when visits are due by the CHW and when a follow-up is needed. In addition to gathering real-time data on the health of the household, the mobile phone monitoring system automatically lists all follow-up visits needed for each week. For example, the CHW is expected to reach all households in their catchment area within a maximum of a 6-month period. Pregnant mothers are to be visited monthly and every 2 weeks within the last 6 weeks of pregnancy. A household with a severely malnourished or stunted child must be visited weekly. A household with a child within one SD of the normal height and weight only needs to be visited monthly. MLHs must be visited more often both in pregnancy and post-birth, especially if there has been no reengagement in care following childbirth (See Table 2).

**Table 2 Tab2:** Identification of responsibility for administrative and implementation functions with community health workers (CHWs)

	Standard Care	Accountable Care
Hiring	Local government	Local government
Salary	Local government	Local government
Training	Initial Philani Intervention Model (PIM) training	Initial PIM training and mobile phones provided
Visit documentation	Log sheet	CHW will log home visits in real time on mobile phones and enter information about the pregnant women in a folder for follow up purposes
Supervision	Local government	PIM
Type of supervision	Log sheet	Random supervision visits every 2 weeks including real-time and data-informed feedback; support and reminders will be sent to CHW and supervisors via mobile phones (“flag system”)

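### CHW phone and folder reports are named as primary-outcome sources, but only the Accountable Care arm records outcome content in them, so gap-filling or informant-swapping with them could work in one arm only

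*Protocol article*

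**What the plan says.** The Primary outcomes section opens with its list of sources: "Self-reports, the Road-to-Health card, and real-time reports by CHWs on mobile phones and in folders will be sources of data". It then ranks them: "Data collected from the assessment team will always be the gold standard, compared to data from the CHWs". For outcomes with more than one source, it plans that "a sensitivity analysis will be conducted to examine whether a different result would have been observed if a different informant had been used". The same section describes the government record used in SC: "The existing CHW reporting system for the government is a log of visits, with little more information than indicating that a visit occurred". It adds that the trial cannot improve that system.

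Table 2 sets the two arms apart. Visit documentation in SC is a log sheet; in AC, "CHW will log home visits in real time on mobile phones and enter information about the pregnant women in a folder". The AC section says what goes into the AC record: visit content and skills, the child's height and weight, and reports on the child grant, immunisations, breastfeeding and HIV care.

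The Assessments section has an independent team measure outcomes in both arms on one schedule, using interviews, health case files and the Road-to-Health card. Table 1 gives the source for each scored indicator and mentions no CHW report.

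On phones, the SC section says "All CHWs will receive a mobile phone and initial Philani training for conducting home visits". The training row of Table 2 has "Initial PIM training and mobile phones provided" in the AC column only.

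**The concern.** A source named for the primary outcomes has outcome content in one arm only. It is written by the workers whose supervision and accountability are the intervention under test. If such a source scores any indicator, the arms are no longer measured in the same way. A difference in recording then cannot be separated from a difference in health, and no analysis after the data are scored can undo that.

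The ranking rule settles disagreement between an assessor and a CHW. It does not say what happens when there is no assessor value. The Power calculations section assumes 80% retention, so about one family in five may lack assessor data at the end. In AC the CHW record could stand in for them; in SC nothing comparable exists. The sensitivity analysis has the same weakness if the CHW is the alternative informant: AC would have data for that comparison and SC would not.

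**Working it through.** **Step 1: the sources side by side.**

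| Place in the protocol article | AC | SC |
|---|---|---|
| Primary outcomes, source list | CHW phone and folder reports included | same list, no distinction by arm |
| Table 2, visit documentation | phone log plus folder | log sheet |
| AC section / Primary outcomes, content | height, weight, child grant, immunisations, breastfeeding, HIV care | "log of visits, with little more information than indicating that a visit occurred" |
| Table 1, sources for scoring | no CHW report | no CHW report |

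The source list and Table 1 do not agree, and the extra source in the list has usable content in AC only.

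**Step 2: where bias could enter.**
- Assessor value present: the ranking rule decides, and the CHW report changes nothing.
- Assessor value absent: the text is silent. Fill-in is possible in AC and not in SC.
- CHW as swapped informant: possible in AC and not in SC. Swaps among Table 1 sources, such as self-report against clinic record, are possible in both arms.

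**Step 3: scale of the fill-in route.** The document gives no figure to reproduce, so this is an illustration.

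Inputs from the document: a composite of 10 indicators (Data analysis); 80% retention, ICC 0.01, alpha 0.05, and a detectable effect of 0.21 (Power calculations); 450 households per arm, with 16 and 21 CHWs (Setting).

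Assumptions: attainment p = 0.7 on each item; inter-item correlation r = 0.1; five items open to fill-in (height, weight, breastfeeding, child adherence through immunisations, maternal adherence through HIV care); all of the 20% lost in AC are filled from CHW records; missing values are otherwise excluded.

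- SD of the composite = sqrt(10 × p(1 − p) × (1 + 9r)) = sqrt(10 × 0.7 × 0.3 × 1.9) = 1.997.
- If CHW records show attainment q, each item shifts by 0.20 × (q − p), and the composite by 5 × 0.20 × (q − p) = q − p points.

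| q in CHW records | Shift per item | Shift in composite | In SD |
|---|---|---|---|
| 0.5 | −4 points | −0.20 | −0.10 |
| 0.6 | −2 points | −0.10 | −0.05 |
| 0.7 | 0 | 0 | 0 |
| 0.8 | +2 points | +0.10 | +0.05 |
| 0.9 | +4 points | +0.20 | +0.10 |
| 1.0 (upper limit) | +6 points | +0.30 | +0.15 |

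The upper limit needs every lost family to be covered and every item reported as attained. Over p = 0.6 to 0.8 and r = 0.05 to 0.2 it runs from 0.09 SD (p = 0.8, r = 0.2: 0.20/2.117) to 0.21 SD (p = 0.6, r = 0.05: 0.40/1.865).

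**Step 4: effect on the test.** Take 360 retained per arm (450 × 0.8), CHW areas as clusters and a two-sided 5% test.
- Variance = [1 + (360/16 − 1) × 0.01]/360 + [1 + (360/21 − 1) × 0.01]/360 = 1.215/360 + 1.161/360 = 0.00660, so SE = 0.081 SD.
- With no true effect, a spurious shift of 0.05 SD gives a false-positive rate of about 9%, and 0.10 SD about 23%. With no fill-in the rate stays at 5%.
- A downward shift of the same size would mask a true benefit.

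**The case against.** The strongest reply is that the protected reading is already on the page. Assessor data always outrank CHW data. Table 1 is introduced as the source list for scoring and contains only assessor-collected sources. Outcomes are measured by an independent team on one schedule in both arms. No passage says that CHW records will replace missing assessor values, and rules for missing data are commonly left to an analysis plan, which is not shown here.

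Much of this stands. Where assessor data exist, a CHW report cannot turn a 0 into a 1. A reader might infer that the intervention itself raises documented attainment in AC; the document does not support that. Nor does it show the direction: AC workers record measured height and weight and flag malnourished or stunted children, so their entries can score 0 as well as 1.

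Two parts of the reply do not close the gap. First, the point is not that a missing-data rule is absent. The article affirmatively names a source with outcome content in one arm only, and that conflicts with Table 1. Second, Table 1 is not a closed list: the Data analysis section gives the child grant and antenatal visits as example indicators, and neither has a row in Table 1. The child grant is among the items that AC workers report by phone.

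A reader might also infer that the informant sensitivity analysis cannot be run in SC at all. That goes too far. Only the version with the CHW as informant lacks an SC counterpart.

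**Conclusion.** The point holds in a limited form. The source list under Primary outcomes includes reports whose outcome content exists in AC only, and it does not match Table 1. The ranking rule protects every value that an assessor collected. It does not cover values that no assessor collected, or the CHW as swapped informant. Both openings exist in AC only and can produce differential ascertainment.

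The size and direction are unknown. The illustrative shifts of −0.10 to +0.10 SD rest on assumed attainment, correlation, number of items, coverage of lost families and CHW-recorded attainment. If CHW data are never used for scoring, the shift is zero.

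A reader might suppose a 10-point rise on five items, which would be 0.50/1.997 = 0.25 SD and above the 0.21 that the trial is powered for. Fill-in for 20% loss cannot produce that when missing values are otherwise excluded: the limit is 0.20 × (1 − p), or 4 to 8 points for attainment of 80% to 60%. Ten points would need missing items to be scored 0, or far more item-level missingness, and the document states neither.

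The phone discrepancy is a separate, plain contradiction. It does not enlarge the bias, because Table 2 gives SC a log sheet whether or not its CHWs hold phones.

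**What to change.** Add one sentence under Primary outcomes: the composite, the individual outcomes and the between-arm informant sensitivity analysis use only sources collected in the same way in both arms by the independent assessors, namely direct measurement, interview, clinic record and Road-to-Health card. State that CHW phone and folder data serve process description, or concordance with assessor data within AC, and never supply an outcome value. Amend the source list in that section to match.

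Separately, reconcile the SC section with Table 2 on which CHWs receive mobile phones.

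The cost is a sentence and no new data. The small downside is that AC values recoverable only from CHW records stay missing, as they would in SC.
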